## Abstract

**Background:**

More than half of all antibiotic prescriptions in general practice are issued for respiratory tract infections (RTIs), despite convincing evidence that many of these infections are caused by viruses. Frequent misuse of antimicrobial agents is of great global health concern, as we face an emerging worldwide threat of bacterial antibiotic resistance. There is an increasing need to identify determinants and patterns of antibiotic prescribing, in order to identify where clinical practice can be improved.

**Methods/Design:**

Approximately 80 peer continuing medical education (CME) groups in southern Norway will be recruited to a cluster randomized trial. Participating groups will be randomized either to an intervention- or a control group. A multifaceted intervention has been tailored, where key components are educational outreach visits to the CME-groups, work-shops, audit and feedback. Prescription Peer Academic Detailers (Rx-PADs), who are trained GPs, will conduct the educational outreach visits. During these visits, evidence-based recommendations of antibiotic prescriptions for RTIs will be presented and software will be handed out for installation in participants PCs, enabling collection of prescription data. These data will subsequently be linked to corresponding data from the Norwegian Prescription Database (NorPD). Individual feedback reports will be sent all participating GPs during and one year after the intervention. Main outcomes are baseline proportion of inappropriate antibiotic prescriptions for RTIs and change in prescription patterns compared to baseline one year after the initiation of the tailored pedagogic intervention.

**Discussion:**

Improvement of prescription patterns in medical practice is a challenging task. A thorough evaluation of guidelines for antibiotic treatment in RTIs may impose important benefits, whereas inappropriate prescribing entails substantial costs, as well as undesirable consequences like development of antibiotic resistance. Our hypothesis is that an educational intervention program will be effective in improving prescription patterns by reducing the total number of antibiotic prescriptions, as well as reducing the amount of broad-spectrum antibiotics, with special emphasis on macrolides.

## Background

Acute respiratory tract infections (RTIs) are important targets for educational strategies aimed at reducing inappropriate prescriptions of antibiotics, because such infections have a high prevalence in general practice [1], and because antibiotics are commonly prescribed even for those illnesses that have a predominantly viral etiology, such as common colds and acute bronchitis [2-4].

Inappropriate use of antibiotics is of great public health concern, both nationally and globally, because of its association with increased antibiotic resistance in the community [5,6]. Bacterial strains that are increasingly resistant to antimicrobial agents pose a severe health threat, and of particular concern is community-acquired infections caused by multi-drug-resistant *Streptococcus pneumoniae *[7,8], macrolide-resistant *Streptococcus pyogenes *[9-11], and methicillin-resistant *Staphylococcus aureus *[12,13].

Antimicrobial resistance is an increasing problem worldwide, and several countries have implemented surveillance systems in recent years. The Norwegian surveillance program for antimicrobial resistance (NORM) was established in 1999 and has reported yearly on the epidemiology of antimicrobial resistance and the usage of antimicrobial agents [14]. Antimicrobial susceptibility data on common pathogens such as *Klebsiella *species, *Haemophilus influenzae*, *Staphylococcus aureus*, and *Streptococcus pyogenes *confirm that antimicrobial resistance is still a limited problem in Norway [15]. This also applies for the prevalence of macrolide-resistant *Streptococcus pneumoniae *(MRSP), which has increased dramatically in several European countries [16], but is still a relatively limited problem in Northern Europe [17,18].

Low levels of antimicrobial resistance in Scandinavian countries is probably due to relatively conservative antimicrobial prescription patterns, compared to southern Europe and USA [19]. Nevertheless, an increase in macrolide resistance in *Streptococcus pneumoniae *blood culture isolates has also been observed in Norway; from 2.4% in 2000, 4.8% in 2002 and 6.0% in 2003, to 9.7% in 2004 [14]. Macrolides are recommended as second-line alternatives in the treatment of RTIs, because the prevalence of non-penicillin-susceptible *Streptococcus pneumoniae *is below 3% in Norway [20]. They are recommended only for patients who are allergic to penicillin or are suspected of having atypical pneumonia or pertussis. Thus, the increase in MRSP is of clinical concern as well as public health interest.

In Norway, more than 90% of all antibiotic prescriptions are issued by general practitioners (GPs) [21], and 60% of these prescriptions are issued as treatment for common RTIs, for which the Norwegian national guidelines recommend penicillin V as the drug of choice [22]. Generally, the number of antibiotic prescriptions has raised with more than 30% in Norway during the last two decades [21].

Norwegian GPs' prescription patterns of antibiotics were studied (1988–89) in the Norwegian county of Møre and Romsdal [4,23], where more than 95% of the GPs in the county participated in the survey. Of all RTIs, acute bronchitis, otitis, and upper respiratory tract infection were the most frequently recorded diagnoses that prompted an antibiotic prescription. Penicillin V was the most commonly prescribed antibiotic for patients suffering otitis, upper respiratory tract infection, tonsillitis, and sinusitis, whereas erythromycin and tetracyclines were most frequently prescribed for lower RTIs [4]. Seven out of 10 children (aged 0–12 years) who were prescribed an antibiotic, received it as a result of a RTI [23]. More than eight out of 10 children who consulted a GP for sinusitis, tonsillitis, acute bronchitis, or pneumonia were prescribed an antibiotic [23]. For ear infections, an antibiotic prescription was given in 44% of all consultations, but this proportion increased to 64% when follow-up contacts for this diagnosis were excluded [23]. Penicillin V was the most frequently prescribed antibiotic for children with ear infection, upper respiratory tract infection, tonsillitis, sinusitis, and skin infections, whereas erythromycin was given to a considerable proportion of those with bronchitis or pneumonia [23].

Acute otitis media (AOM) is the most common bacterial infection in children [24]. In the Western world, most cases of AOM remit spontaneously and without complications [25]. The prevalence of antibiotic treatment for AOM varies in different countries, between 31% in The Netherlands and 98% in USA, Australia and New Zealand [26]. In The Netherlands, treatment of symptoms without antimicrobials has been adopted as the routine initial treatment for otitis media, and this policy is associated with decreased emergence of resistance among organisms commonly found in AOM [27]. In a meta-analysis, Del Mar et al. [28] concluded that early use of antibiotics provided only modest benefit for AOM, and that 17 children with AOM must be treated with antibiotics in order to prevent one child from experiencing pain 2–7 days after presentation of symptoms. It is likely that AOM is the reason for many unnecessary prescriptions for antibiotics, especially when broad-spectrum antibiotics are used [26]. In a study from a Norwegian emergency department setting, 90% of 819 children (aged 1–15 years) with AOM received treatment with antibiotics, and 18% of these prescriptions where for antibiotics other than penicillin V [29].

Sinusitis represents a complicated and multifaceted group of diseases that is generally classified into the categories of acute and chronic [30]. The diagnosis of acute sinusitis in GP settings is a challenging task [31], and although many instances of acute sinusitis are of bacterial origin, most cases are thought to be inflammatory rather than infectious [30]. The issues of the pathogenesis and treatment of sinusitis are ongoing areas of controversy and active investigation [30,31].

Steinman et al. [32] found that broad-spectrum antibiotics were prescribed in more than half of all cases of RTIs in adults, and that there was a wide variation in prescribing of such agents among different groups of patients and physicians, even after controlling for diagnosis and comorbidities. In a large, cross-national database study of antibiotic use and its associations with resistance, Goossens et al. [33] investigated outpatient antibiotic use in 26 countries in Europe that provided internationally comparable distribution or reimbursement data in the period 1997–2002, and found that prescription patterns varied greatly; the highest rate was in France and the lowest was in The Netherlands. A shift from the old narrow-spectrum antibiotics to the new broad-spectrum antibiotics (like the newer macrolides) were observed, as well as striking seasonal fluctuations with winter peaks in countries with high yearly use of antibiotics [33].

The use of macrolides for common airways infections deviate from current Norwegian national guidelines [34,35], and Brubakk and Bruun [36] underline that indications for macrolides in airway illnesses are limited to infections with *Bordetella pertussis *and *Mycoplasma pneumonia*.

In outpatients, macrolide consumption is closely linked to the development of streptococcal resistance. In Finland, there was a steady and statistically significant decline in erythromycin resistance among *group A streptococcal *isolates from throat-swab and pus samples after a reduction in the use of macrolide antibiotics in outpatient therapy [37]. Evidence from Sweden and New Zealand also demonstrate that a reduction in antibiotic use can be accompanied by a reduction in antibiotic resistance [38,39].

In a recent review issued by the Cochrane Collaboration, Arroll [40] argues that antibiotics have only a limited role in the treatment of AOM, sore throat, acute maxillary sinusitis, common cold, and acute purulent rhinitis. Except for radiologically proven acute maxillary sinusitis, antibiotics are not recommended as initial treatment for any of the conditions mentioned above [40].

Questions on validity and relevance of individual studies that are summarized in systematic reviews may be assessed differently by various reviewer groups, and may explain why the guidelines from the Infectious Disease Society of America (2002) recommend routine treatment for otitis media [41], whereas the Cochrane review represent a more cautious line and remain consistent with the older guidelines in not recommending antibiotics as a first-line treatment [40].

Over the past decade, general practice prescribing of antibiotics to children has halved in England, and this reduction has not been associated with an increase in admission to hospital for possible complications, like peritonsillar abscess or rheumatic fever [42]. The decline in use is due to a substantial reduction in prescriptions by GPs [42]. After 1997, the proportion of prescriptions taken to a pharmacist also declined, possibly indicating that GPs were adopting the "delayed prescribing" policy (issuing prescriptions with advice to parents to wait and see if their child's condition improved spontaneously) that was introduced after widespread dissemination of trial results supporting this practice [43].

An important aspect in the strategy of "delayed prescriptions" is the necessary management of patients' requests for specific treatments. Evidence suggests that a majority of patients feel that antibiotics are an appropriate treatment for a wide range of respiratory tract symptoms, and that doctors will prescribe antibiotics for them [44], despite convincing evidence of only limited antibiotic benefit for such conditions [25,40,45-53].

The first evidence of benefit from a randomized trial of delayed prescriptions for respiratory infections came from a trial of antibiotics for acute sore throat carried out by Little et al. [46], who gave either a prescription for antibiotics to be filled immediately, or one to be filled after three days, or no prescription for antibiotics. The "immediate group" consumed 99% of the antibiotic prescriptions, while the "delayed group" used only 31% with no apparent negative medical consequences [46]. In an other report, Little et al. [54] found evidence that both current and previous antibiotic prescribing for sore throat increased reattendance, and argues that doctors should avoid antibiotics or offer a delayed prescription for most patients with sore throat, in order to avoid medicalising a self-limiting illness.

Both Norwegian [55] and Danish [56] studies show great variation in GPs' prescription patterns for RTIs, and demonstrate a lack of adherence to current guidelines [21]. The potential for improvements are important, because community-wide antibiotic resistance reduces the effectiveness of currently available drugs to combat bacterial pathogens, and increases the individual patient's risk of becoming infected with drug-resistant organisms [57-59]. Previous studies have shown benefit from targeted educational intervention strategies towards GPs. Coenen et al. [60] reported that an (inter)actively delivered tailored intervention implementing a guideline for acute cough in a GP setting was successful for optimizing antibiotic prescribing without affecting patients' symptom resolution. Munck et al. [61] reported that a tailored audit of Danish GPs' antibiotic prescriptions for RTIs through the *Audit Project Odense (APO)*, resulted in a reduction in prescribed antibiotics, and that the large share proportion of broad-spectrum antibiotics was shifted to penicillin. The intervention effect in this study was significant, even two years after the intervention [61].

Welschen et al. [62] conducted a randomized controlled trial aimed at reducing antibiotic prescription rates for RTIs in primary care. The intervention included; a) group education meetings with consensus procedures and communication skills training, monitoring, and feedback on prescribing behaviour for GPs; b) group education for GPs' assistants and for pharmacists; and c) education materials for patients. At baseline, antibiotic prescription rates for RTIs were almost similar in the intervention and the control groups (27% and 29% respectively). Following the intervention, the prescribing rate in the intervention group fell to 23%, whereas it increased to 37% in the control group (mean difference of change; – 12%). The intervention did not influence patients' satisfaction or hospital referral rates [62].

Flottorp et al. [63] conducted a multifaceted intervention in 142 general practices to improve the management of urinary tract infections (in women), and sore throat. The intervention was based on patient educational material, computer based decision support and reminders, an increase in the fee for telephone consultations, and interactive courses for general practitioners and practice assistants. In this study patients in the sore throat group were 3% less likely to receive antibiotics after the intervention, compared to the control group [63].

In the Norwegian *Møre & Romsdal Prescription Study*, Rokstad et al. [64] performed a controlled educational intervention towards GPs, aimed at improving prescriptions for acute cystitis and insomnia. Their intervention included mailed prescription feedback along with printed therapeutic recommendations, and resulted in statistical significant (although clinically moderate) improvements in prescription patterns in the intervention group (GPs in one district), compared to the control group (GPs in another district) [64].

Eisenberg [65] has suggested that the core principle of effective feedback is individualized feedback with information on behaviour compared with specific standards: It seems as if such feedback is more effective when delivered face-to-face [65,66].

The results of evaluations of interventions to improve clinical practice vary and large effects are rarely seen [67,68]. Several educational strategies have been used. Davies et al. [69] reviewed 777 continuous medical education (CME) studies and found evidence that educational intervention consisting of passive dissemination of clinical practice guidelines had only little or no effects on practice. This corresponds with later reports by Oxman et al. [70] and Freemantle et al. [71]. Other, more active strategies, like educational outreach visits [72] and multifaceted interventions [67], are more effective, but will generally require more resources [67]. Soumerai et al. [73] reviewed educational methods for improving prescribing in primary care, and examined the approaches of feedback to prescribers, mailed-out educational material, group education and educational outreach (academic detailing), with educational outreach having the largest impact [66]. In an extensive review, Jamtvedt et al. [74] concluded that audit and feedback may be effective for improving professional medical practice, although the effects are generally small to moderate. Absolute effects of audit and feedback are more likely to be large when baseline adherence to recommended practice is low [74].

Underlying reasons for deviations between clinical practice and clinical guidelines vary from one problem to another and from one physician to another [70]. Therefore, it is recommended to address potential barriers to change when tailoring an intervention targeting change in medical performance. Because non-equivalent comparison groups may distort the results of evaluations, cluster-randomized trials (in which healthcare professionals or groups of professionals, rather than patients are randomized) are more likely to provide valid results than other research designs, such as controlled before-after or time-series studies [75].

### Objectives

The primary objective of this trial is to evaluate the effects of a tailored intervention towards Norwegian GPs for a more rational approach to antibiotic prescriptions for RTIs. Our hypothesis is that an educational intervention program carried out during a 6-month period will be effective in improving prescribing patterns by reducing the total number of antibiotic prescriptions, as well as reducing the relative amount of broad-spectrum antibiotics, with special emphasis on macrolides. Degree of improvement will be measured by prevalence of specific antibiotic prescriptions and the combination of particular antibiotic prescriptions and selected diagnostic codes, according to the International Classification of Primary Care (ICPC-2) [76]. Secondary objectives are to estimate the agreement between prescribed and actually dispensed drugs, the latter based on dispensed drugs recorded in the Norwegian Prescription Database (NorPD), a national registry including data for all prescription drugs issued at Norwegian pharmacies, established in 2004 [77]. We will also explore effect of "delayed prescriptions" on the antibiotic prescription patterns.

## Methods/Design

Our main hypothesis will be tested using a cluster-randomized controlled trial comparing outcomes between the intervention and control groups at follow-up. The clusters are existing peer CME groups, comprised by GP specialists. These groups of GPs will be randomized to receive a tailored intervention to support a more rational antibiotic prescribing for RTIs, or to a control group.

Prescription data will be collected for all eligible patients from intervention and control groups at baseline and one year after the initiation of the trial.

### Participants

In Norway, specialists in general practice must renew their clinical specialty every five years. In this renewal process, participation in a number of peer CME group meetings are compulsory, in order to stimulate a continuously medical education and reflection.

GP's in the same practice usually attend the same peer group, according to information from the Norwegian Medical Association. All peer groups (approximately 250) on average consisting of seven to eight colleagues located in the southern part of Norway, will be invited to participate in this trial. Our aim is to recruit approximately 80 peer groups or more to the current trial. Participating practitioners using one of four major electronic patient record (EPR) systems (Infodoc^®^, WinMed^®^, ProfDoc Vision^® ^or System X^®^) are eligible for the trial. More than nine out of ten of Norwegian general practices use one of these four EPRs, which are used routinely during consultations with patients [78].

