### Intervention

We have developed an intervention through a process of identifying inappropriate prescriptions of antibiotics for RTIs; either as particular drugs, or drugs linked to specific diagnosis. Identification of irrational antibiotic treatment is based on guidelines on antibiotic prescriptions issued by The Norwegian Board of Health 2000 [35]. This guideline was distributed to all Norwegian GPs in 2000 and is also available on the Internet. Examples of suboptimal antibiotic prescribing according to this guideline are listed in Table 1.

In order to implement a more rational prescribing, 13 GPs will be recruited as tutors, each with responsibility for the intervention in three peer CME groups. Each tutor, named Prescription Peer Academic Detailer (Rx-PAD), will receive a four days' pre-study training program, focusing on the evidence of antibiotic treatment of RTI, pedagogical intervention techniques, and how to install and use the data-software program for data collection. When recruiting Rx-PADs, emphasis is also laid on the economic independence from any pharmaceutical manufacturers.

The tailored intervention towards the GPs in the peer groups will include two educational outreach visits, both performed by the same Rx-PAD. The elements of the intervention are discussions within the peer group, collection of individual prescription data, audit based on individual feedback reports, as well as a one day regional work-shop, see Figure 1.

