### Recruitment and randomization

Block-randomization of peer CME groups will be done within geographical strata, each comprised of one or more counties. The size of the blocks will vary according to the number of recruited groups within each stratum. An independent researcher not involved in the study will be responsible for the randomization. Based on this randomization, peer groups will be assigned to either the intervention group or to the control group.

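### Peer groups that share a practice can be randomised to opposite arms, which allows a small, avoidable bias toward no effect

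*Protocol article*

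**What the plan says.** The unit of randomisation is fixed in Methods/Design: "The clusters are existing peer CME groups, comprised by GP specialists". Participants sets out who is approached: "All peer groups (approximately 250) on average consisting of seven to eight colleagues located in the southern part of Norway, will be invited". The only stated eligibility condition is that the practitioner uses one of four named electronic record systems. On practices, the same section says: "GP's in the same practice usually attend the same peer group, according to information from the Norwegian Medical Association".

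Recruitment and randomization describes blocks of peer groups within strata of one or more counties, and then: "Based on this randomization, peer groups will be assigned to either the intervention group or to the control group". It has no provision for groups linked through a practice.

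Sample size and statistics bases its calculation on a control prevalence that stays at 27%. The Discussion says that the control arm receives no antibiotic intervention, names the clinic as one of three levels of clustering behind the ICC, and covers a possible Hawthorne effect by a comparison with GPs outside the trial in the prescription database. It does not discuss exposure through a shared practice.

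On tutors, Intervention says: "13 GPs will be recruited as tutors, each with responsibility for the intervention in three peer CME groups". It does not say which peer groups, if any, the tutors themselves attend.

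**The concern.** Randomising by peer group limits contamination to the extent that practices lie wholly inside one group. The word *usually* admits that some do not. Two groups that share a practice will normally lie in the same area, and so in the same stratum, where blocking ensures that both arms occur. Nothing stated prevents a split.

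In a split practice the control GP works beside someone who has had the outreach visits, the feedback discussion, the workshop and the delayed-prescription option. Treatment advice of this kind passes easily between colleagues. Any uptake lowers the control rate below the assumed 27% and pulls the estimated effect toward zero. Recruiting more groups restores power but does not remove the bias. Once allocation has been done, the split cannot be repaired without giving up part of the randomised comparison.

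**Working it through.** **Inputs from Sample size and statistics:** 27% versus 18%; ICC 0.085; 7 GPs × 300 cases = 2100 cases per group; 80% power; 5% significance level (taken as two-sided). **From Participants:** about 250 groups invited, about 80 sought. Equal arms of about 40 are assumed.

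**1. The plan's own figure.** The variance inflation factor is 1 + (2100 − 1) × 0.085 = 179.4; the article gives 179. The two-proportion formula with continuity correction gives 359 independent cases per arm, and 359 × 179.4 / 2100 = 30.7, rounded up to 31 groups per arm. The stated 31 reproduces, so 62 are required in all.

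**2. What share of control GPs could be exposed?** The article gives no figure. For a practice-mate's different group to be in the intervention arm, it must be recruited (80/250 = 32%) and fall in that arm (about one half): 0.32 × 0.5 = 0.16. To expose a share *e* of control GPs, the share of GPs with practice-mates in another group would have to be about *e* / 0.16:

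- 5% exposed: 0.05 / 0.16 = 31% of GPs
- 10% exposed: 0.10 / 0.16 = 63%
- 20% exposed: 0.20 / 0.16 = 125%, which is impossible

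These needed shares fall if linked groups tend to join together. If the other group always joined, the factor would be 0.5 and they would be 10%, 20% and 40%. Given *usually*, 5% to 10% exposed is probably at the high end and 20% is not credible.

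**3. Dilution.** Loss = 9 points × share exposed × share of the effect taken up.

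- Low: 9 × 0.05 × 0.30 = 0.14 points (1.5% of the effect)
- High: 9 × 0.10 × 0.60 = 0.54 points (6% of the effect)

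**4. Power.** Control rate = 27% − loss, intervention rate 18%, effective size per arm = groups × 2100 / 179.4. Normal approximation without continuity correction, which is why 31 groups show 83% and not 80%:

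| Loss (points) | Contrast | Power, 31 per arm | Power, 40 per arm | Groups needed per arm (continuity-corrected) |
|---|---|---|---|---|
| 0 | 9.0 | 83% | 91% | 31 |
| 0.14 | 8.9 | 82% | 90% | 32 |
| 0.54 | 8.5 | 78% | 88% | 35 |

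At about 40 per arm, power stays at 80% or more until about 15% of the effect leaks (81% at 15%, 76% at 20%).

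**5. Tutors.** If all 13 belonged to recruited groups, 13/80 = 16% of groups would hold one. If they came at random from the 250, then 13 × 80/250 / 2 = 2.1 control groups would, or about 5% of 40. If only the tutor's own prescribing changed, at full effect and as one of 7 GPs, the loss would be 9 × 0.16 / 7 = 0.2 points in the first case and 9 × 0.052 / 7 = 0.07 in the second.

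**The case against.** The peer group is itself the safeguard. It is an existing unit that in most cases already holds the practice-mates, and randomising it is the standard way to limit contamination. Leakage needs a practice that spans groups, a second group that joins, and opposite allocation. Software and feedback reports go to the individual participant, so a control colleague does not receive them merely by sharing premises. Any dilution is conservative, and planned recruitment exceeds the requirement. All of this stands, and it is why the effect is small. It does not remove the point: the exception is conceded in the text and the allocation rule ignores it. The comparison with outside GPs does not close the gap either. By the Discussion's own account those data have no link to diagnoses. They might reveal a shift in controls but cannot correct the randomised contrast for RTIs.

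Two stronger readings are tempting. A reader might infer that contamination leaves the trial underpowered. The figures do not support this, since power at about 40 per arm remains near 88% even at the upper assumption. A reader might also infer that trained tutors sit in randomised control groups, because all groups are invited and "participation in a number of peer CME group meetings are compulsory" for specialists renewing their specialty. The article does not say where tutors come from, and a full protocol may settle it. That remains a possibility and is not a stated feature of the design.

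**Conclusion.** The point holds for practices that span peer groups. The stated allocation rule lets such groups fall in opposite arms, contrary to the assumption of an unaffected control rate. The likely size is a bias toward no effect of about 0.1 to 0.5 points out of 9. This rests on assumed exposure of 5% to 10% of control GPs and uptake of 30% to 60% of the effect, neither of which the article gives. The sample size of 31 groups per arm is not in error, and power is not the problem. Tutors are a minor addition, conditional on facts that the article does not state.

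**What to change.** In Participants, add that each GP's practice is recorded at recruitment. In Recruitment and randomization, add that peer groups sharing a practice are identified before allocation and randomised together as one unit within their stratum. Analyse such a unit as a single cluster.

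If any tutor belongs to a recruited peer group, settle before allocation that the group is not randomised. This is better than dropping its data afterwards, which would alter the randomised set.

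The cost is one question at recruitment, two or three sentences, and slightly fewer independent units of less even size. The margin of 80 − 62 = 18 groups can absorb this. At most 13 of about 250 invited groups would be lost on account of tutors. The change is useful only if it is made before allocation.
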